#### **Patient selection:**

**Inclusion criteria:** 1. Age > 18 years. 2. Reducible, primary inguinal hernia. 3. The patient accepts participation and is capable of giving informed consent.

**Exclusion criteria:** 1. Female. 2. Recurrent hernia. 3. Femoral hernia. 4. Ongoing anticoagulant medication. 5. Current obvious drug abuse. 6. ASA group 3-6

**Surgical material and technique:** The anterior tension-free mesh repair according to Lichtenstein will be performed under local anaesthesia using a sterilized low cost mesh. The mesh is made of lightweight polyethylene. Prior to the operation, the mesh will be cut into 10x15 cm strips. Thereafter the mesh will be cleaned using water and a mild detergent, packed and autoclaved at 121 degrees Celsius for 20 minutes. This has been shown to ensure adequate sterility and minimal changes to the mesh.(37) Preoperatively, the patients will be given one prophylactic dose of 1.5 grams of Flucloxacillin orally. Local pre-operative routines for elective hernia surgery will be

187 followed. The World Health Organisation (WHO) surgical safety checklist for surgery  
188 will be used for all surgeries.

189 ***Surgical training:*** Certified consultant surgeons (the trainers) will train the surgical-  
190 assistant CHOs and the medical officers (the trainees) in tension-free mesh hernia  
191 repair. Only trainees currently performing and proficient in open tissue inguinal  
192 hernia repair will be trained. Trainees will attend a two-week training course  
193 including lectures on mesh repair and local anesthesia administration for inguinal  
194 hernia repair. Trainees will observe five mesh inguinal hernia repairs and perform  
195 three mesh repairs under supervision by the trainers. After the training, two trainers  
196 will independently assess trainee operative skills using a checklist based on the  
197 American Board of Surgery Operative Performance Assessment Form for open  
198 inguinal hernia.(38) Upon successful completion of the assessment, enrollment of  
199 patients into the study will begin. A minimum of five surgical assistants CHO and  
200 five medical officers will be included.

201 ***Data collection:*** Data will be collected on the previous educational and surgical  
202 experience of each hernia surgery trainee as well as the specifics of their training in  
203 mesh hernia repair for this study (number of procedures observed, performed under  
204 supervision, and practical test scores). Patient interviews including medical history,  
205 the EuroQol 5D (EQ5D) and the Inguinal Pain Questionnaire (IPQ) will be done  
206 preoperatively, at follow up two weeks and one year after surgery. Physical  
207 examination will be undertaken preoperatively in conjunction with the interviews to  
208 verify that the patients meet the inclusion criteria, and also at two weeks and one year  
209 postoperatively in order to detect post operative complications and recurrences.  
210 Expenses associated with the training and the surgeries will be recorded.

211 ***Data analysis:*** Surgical trainee data will be analysed descriptively. Primary endpoints  
212 for patient data include hernia recurrence. Secondary endpoints include postoperative  
213 complications, chronic pain and patient satisfaction. The outcomes following surgery  
214 performed by medical doctors and CHOs will be compared. Results from Sierra  
215 Leone will be compared with results from the other collaborating centres. When  
216 comparing data, two sample t-tests will be used for continuous variables and  
217 Pearson's Chi-square or Fisher exact test will be used for counts. A p-value < 0.05  
218 will be considered statistically significant.

219 Cost effectiveness will be expressed as USD per Disability Adjusted Life Year  
220 (DALY) averted and USD per Quality Adjusted Life Year (QALY) gained. The  
221 EuroQol questionnaire will be used to calculate QALYs gained (before surgery  
222 compared to one year postoperatively).(39) The Inguinal Pain Questionnaire results  
223 will be used to calculate DALYs gained (before surgery compared to one year  
224 postoperatively).(40)

225 The cost analysis will be done from the care provider's perspective. It will include  
226 staff time, material consumption in relation to the surgery as well as hospital overhead  
227 costs and capital costs.

228 Disability weights for the DALY calculation will be achieved by converting the  
229 results from the seven-level IPQ into the three-level disability weights for  
230 abdominopelvic as outlined in the Global Burden of Disease study 2010.(41) The  
231 disability weight one year after the surgery will be subtracted from the disability  
232 weight before the surgery. DALYs averted will be calculated by multiplying the  
233 disability weight difference with the remaining life expectancy of the patient

according to the WHO life table for Sierra Leone.(42) The mean DALYs averted will be presented.

QALYs gained will be calculated by translating the results from the EQ5D questionnaires into index values. The difference in the index value before and one year after the surgery will be multiplied with the remaining life expectancy of the patient. The mean QALYs gained will be presented.

In line with the Global Burden of Disease study 2010, no time and age weighting will be used.(41) A sensitivity analysis will be undertaken to assess the robustness of the assumptions.

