#### Method

**Study design:** Single-blinded, randomised clinical trial

**Study population:** The project will be undertaken in two hospitals in northern Sierra Leone – Kamakwie Wesleyan Hospital and Masanga Hospital, both longstanding partner hospitals in CapaCare's Surgical Training Programme.

**Sample size calculation:** *Statistical rationale:* Based on a non inferiority design the assumptions are as follows: 80% power, 5% significance level, 5% non-inferiority limit and expected success rate of 98% in both arms results in a sample size of 97 individuals in each group. Correcting for an expected 15% loss to follow up we adjust the sample size to 114 in each group, or 228 in total.

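### Operators are nested in arm, with only five per cadre guaranteed, yet the sample size and the named tests treat patients as independent; the stated 80% power and the p-values are too favourable by an amount that depends on an unstated ICC

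*Protocol*

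**What the plan says.** Aim 2 (Protocol, section 3) asks whether non-physician clinicians and doctors achieve comparable outcomes, and the Data analysis paragraph of section 4.1 compares results between these two cadres. On operator numbers, the Surgical training paragraph of section 4.1 says "A minimum of five surgical assistants CHO and" then gives the same minimum for medical officers. It sets no number or limit of cases per operator.

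The sample size paragraph opens "Based on a non inferiority design the assumptions are as follows" and lists "80% power, 5% significance level, 5% non-inferiority limit" together with 98% expected success in both arms, which "results in a sample size of 97 individuals in each group". The only adjustment is for 15% loss to follow-up, giving 114 per group.

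For the comparison, the Data analysis paragraph states that "two sample t-tests will be used for continuous variables and" Pearson chi-square or Fisher exact tests for counts. Data on the operators themselves are to be described only. Recurrence is the primary endpoint. Complications, chronic pain and satisfaction are secondary.

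**The concern.** A CHO cannot also be a medical officer, so each operator contributes patients to one arm only. Patients of the same operator share that operator's skill and habits, so their outcomes may be correlated. Randomising patients balances the patients; it does not remove variation between operators from the comparison of cadres. The protocol wants to generalise beyond the operators in the trial: its Introduction speaks of large-scale implementation, and section 4.3 of influencing national policy on training.

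Any positive correlation within operator makes the true standard error of the cadre difference larger than the one these methods assume. A non-inferiority claim could then pass too easily, or a secondary difference could reflect one strong or weak operator rather than a cadre. The protocol itself fixes the independence-based sample size and tests, so this is not merely detail left to an analysis plan.

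**Working it through.** **Inputs from the protocol:** 98% success in both arms, 5-point margin, 80% power, 5% significance, 97 evaluable per group, at least five operators per cadre. **Assumption, not in the protocol:** operator ICC of 0.005, 0.01, 0.02 or 0.05.

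**1. Reproduce the stated figure.** For independent patients, n = (z₁₋α + z₀.₈)² × 2 × 0.98 × 0.02 / 0.05². At one-sided 5%: (1.645 + 0.842)² × 0.0392 / 0.0025 = 96.9, so 97. (One-sided 2.5% gives 124, which does not match.) Loss to follow-up: 97 / 0.85 = 114.1. The stated size is therefore exactly the independent-patient result and contains no allowance for operators.

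**2. Design effect.** With five operators and equal caseload, m = 97 / 5 = 19.4 and DE = 1 + (19.4 − 1) × ICC.

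**3. Power when the variance reflects operators.** Power = Φ(0.05 / √(0.0392 × DE / 97) − 1.645). With DE = 1 this is Φ(2.487 − 1.645) = 80.0%. With ten operators per arm, m = 9.7 and DE = 1 + 8.7 × ICC.

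**4. Error of a t-test that ignores operators.** True two-sided error = 2 × [1 − Φ(1.96 / √DE)].

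| ICC | DE, five per arm | Effective n per arm (97/DE) | Power, five per arm | Power, ten per arm | True error of nominal 5% t-test, five per arm |
|---|---|---|---|---|---|
| 0 | 1.00 | 97 | 80% | 80% | 5% |
| 0.005 | 1.09 | 89 | 77% | 79% | 6% |
| 0.01 | 1.18 | 82 | 74% | 77% | 7% |
| 0.02 | 1.37 | 71 | 69% | 74% | 9% |
| 0.05 | 1.92 | 50 | 56% | 67% | 16% |

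**5. Primary endpoint, simulated.** Beta-binomial operator effects, five operators per arm (20, 20, 19, 19, 19 patients), 200,000 runs. False non-inferiority is evaluated at the margin (7% against 2% recurrence) with one-sided 5% limits.

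| ICC | Wald limit ignoring operators | Score-type limit ignoring operators | Operator summaries, 8 df |
|---|---|---|---|
| 0 | 7.7% | 4.3% | 6.0% |
| 0.005 | 8.8% | not computed | 6.4% |
| 0.01 | 9.6% | 5.8% | 6.6% |
| 0.02 | 11.3% | 6.9% | 7.3% |
| 0.05 | 16% | 10.7% | 9.2% |

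Each column must be read against its own first row. The Wald limit is already too liberal without clustering, so at ICC 0.01 clustering adds about 2 points to it. Simulated power at 98% in both arms with the Wald limit ignoring operators is 81, 80, 80, 79 and 77% down the rows, so it hardly moves.

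**6. Why recurrence is awkward.** Expected events per arm are 97 × 0.02 = 1.9. An operator with 19.4 patients has no recurrence with probability 0.98^19.4 = 0.68, so about 3.4 of five operators per arm have none. Even without clustering, at least one arm has no recurrence in 1 − (1 − 0.98^97)² = 26% of trials.

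**7. Uneven caseload.** This is an illustration that the protocol does not exclude. If one operator per arm treats 57 of 97 patients and four treat 10 each, m becomes (57² + 4 × 10²) / 97 = 37.6. Power is then about 69, 60 and 43% at ICC 0.01, 0.02 and 0.05.

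**The case against.** The strongest reply is that the size is unknown. No ICC is given, recurrence is rare and its ICC may be small. Trainees must already be proficient and must pass an assessment by two trainers, which may narrow operator differences. Five is a minimum, and more operators shrink the effect. An operator-adjusted analysis could also sit in an analysis plan that is not shown. All of this stands as a limit on magnitude. It does not change the direction, it applies less to pain, complications and satisfaction, and a later analysis plan cannot restore the 80% power claimed here.

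A second reply, also correct, is that the usual remedy does not serve the primary endpoint well. Operator-level summaries on 8 df give 6.0 to 9.2% false non-inferiority over the range, above 5% even at ICC 0. GEE or mixed models may not be estimable with so few events.

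A reader might infer several stronger things that the protocol does not support:

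- That power loss and error inflation occur together. They belong to different analyses: power falls if the analysis carries the operator variance, and errors rise if it does not.
- That the trial carries the information of ten operators rather than 194 patients. At ICC 0.01 the effective size is still 82 per arm.
- That reported intervals will be too narrow. The protocol mentions no confidence intervals; the point concerns standard errors and p-values.
- That one operator will dominate an arm. The protocol merely does not prevent it.

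**Conclusion.** The omission is real and visible in the text: at least five operators per cadre, each nested in one arm, with a sample size and tests built for independent patients. With five operators per arm and even caseloads, the 80% power is really about 77% at an ICC of 0.005 and about 56% at 0.05 if the analysis accounts for operators. If it does not, the cost appears as false positives on secondary endpoints and false non-inferiority on recurrence. At an ICC of 0.01 or below the effect is modest; at 0.05 it is serious, and ten operators per arm would reduce but not remove it. Because the size rests wholly on an assumed ICC, this is a point that should be fixed. It does not show that the trial's main conclusion would be invalid.

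**What to change.** - **Sample size paragraph:** restate power over an assumed ICC range and the planned number of operators, in place of a single 80%. No added enrolment is asked for. With five operators fixed, the evaluable number per arm needed for 80% power, 97 × (1 − ICC) / (1 − 97 × ICC / 5), is about 120 at ICC 0.01 but about 3,070 at 0.05, so extra patients under the same operators soon stop helping.
- **Secondary endpoints:** record the operator for each patient and compare cadres with operator as the cluster and a small-sample correction. Operator-level summaries with 8 df (5 + 5 − 2) would do when there are five per arm.
- **Recurrence:** report the non-inferiority limit from a score-type method as the main figure, with an operator-clustered sensitivity analysis and a table of recurrences by operator. The score-type limit does not itself absorb clustering, so both are needed.
- **Caseload:** spread allocated cases about evenly, roughly 114 / 5 = 23 per operator if there are five per arm. This must be arranged before or during enrolment, because it cannot be recovered afterwards.

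The cost is some analysis wording, one recorded variable and scheduling effort. The downside is wider intervals and a less favourable stated power.

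### The unadjusted two-sample t-test, the only method named for continuous variables, forgoes precision that the preoperative EQ5D and IPQ would give the doctor versus CHO comparison

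*Protocol*

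**What the plan says.** All of this is in Protocol section 4.1, under Method.

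- **Collection.** Data collection states that "the EuroQol 5D (EQ5D) and the Inguinal Pain Questionnaire (IPQ) will be done" at three times: "preoperatively, at follow up two weeks and one year after surgery. Physical" examination is the next topic. Each patient interviewed therefore has a preoperative value of both scales.
- **Endpoints.** The primary endpoint is recurrence: "for patient data include hernia recurrence. Secondary endpoints include postoperative" "complications, chronic pain and patient satisfaction. The outcomes following surgery". The EQ5D is not in this list.
- **Comparisons.** Two are named, both between separate groups of patients. Outcomes after surgery "performed by medical doctors and CHOs will be compared. Results from Sierra" "Leone will be compared with results from the other collaborating centres. When" opens the sentence on tests.
- **Test.** That sentence runs "comparing data, two sample t-tests will be used for continuous variables and" then gives chi-square or Fisher tests for counts and a 0.05 threshold. No covariate or baseline term is mentioned.
- **Before-after quantities.** These are described separately: "EuroQol questionnaire will be used to calculate QALYs gained (before surgery" against one year after). The preoperative and one-year EQ5D index values, or disability weights from the IPQ, are subtracted and multiplied by the patient's remaining life expectancy. The mean is then presented.

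**The concern.** A preoperative value of the same scale is often the most useful covariate for a one-year patient-reported score. Here it is collected anyway, but the only test named for continuous variables does not adjust for it. Aim 2 asks whether the two cadres deliver comparable outcomes, so the comparison of medical officers with CHOs is where precision matters. An avoidably wide confidence interval for the difference in the EQ5D index, or in pain if the IPQ is analysed as a score, makes comparability harder to show and a real difference harder to see. What is at stake is efficiency in secondary and economic outcomes.

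**Working it through.** **The plan's own figure.** The only sample size stated is for the binary endpoint: 98% success in both arms, 5-point margin, 80% power, 5% significance. With a one-sided 5% level, n = (1.645 + 0.842)² × 2 × 0.98 × 0.02 / 0.05² ≈ 96.9, so 97 per group, as stated. Then 97/0.85 = 114.1, against the stated 114. No continuous outcome enters this, so nothing below changes the sample size.

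**Inputs for the precision check.**
- n = 97 evaluable patients per arm (Protocol, Sample size calculation).
- r, the correlation of preoperative and one-year values: not given; assumed 0.1, 0.3 and 0.5.
- SD: not given; results are in SD units, with the same SD at both times.
- Patients independent; two-sided 5%; 80% power.

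**Variance of the between-arm difference (SD = σ).**
- t-test on one-year values: 2σ²/n.
- t-test on change from baseline: 2(1 - r) × 2σ²/n.
- ANCOVA on the preoperative value: (1 - r²) × 2σ²/n.

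ANCOVA relative to one-year values is therefore 1 - r². Relative to change it is (1 - r²)/(2(1 - r)) = (1 + r)/2.

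**Detectable difference.** For one-year values it is (1.960 + 0.842) × √(2/97) = 2.802 × 0.1436 = 0.402 SD. The other methods multiply this by the square root of their variance factor.

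| Assumed r | ANCOVA / one-year t-test | ANCOVA / change t-test | Detectable: one-year t-test | Detectable: change t-test | Detectable: ANCOVA |
|---|---|---|---|---|---|
| 0.1 | 0.99 | 0.55 | 0.402 | 0.540 | 0.400 |
| 0.3 | 0.91 | 0.65 | 0.402 | 0.476 | 0.384 |
| 0.5 | 0.75 | 0.75 | 0.402 | 0.402 | 0.348 |

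**In patients.** The gain over the one-year t-test equals having 1/0.99 = 1.01, 1/0.91 = 1.10 or 1/0.75 = 1.33 times as many patients. Power for a 0.4 SD difference is 79.6% with the one-year t-test, against 83.2% (r = 0.3) and 89.6% (r = 0.5) with ANCOVA.

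**If the SD differs between times.** The factor 1 - r² still holds. The factor (1 + r)/2 does not. However, with SDs s₀ (before) and s₁ (after), the change-score variance exceeds the ANCOVA variance by a multiple of (s₀ - r·s₁)², which is never negative. ANCOVA is thus no worse than either t-test, apart from the one degree of freedom spent on the slope.

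**The case against.** **Covariate adjustment is usually left to the SAP, which is not shown.** True in general. Here, though, the protocol does not leave the method open: it names the t-test for continuous variables. An SAP that used ANCOVA would depart from that text.

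**The t-test is valid.** This stands. Between randomised arms it is unbiased, and chance baseline imbalance is already reflected in its standard error. The point is about precision only.

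**A t-test on each patient's change also fits the text and uses the baseline.** Correct, so it cannot be said that every continuous comparison ignores the baseline. But this does not recover the loss. At equal SDs the change score is less precise than the one-year value alone when r is below 0.5, and ANCOVA is more precise than either.

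**The comparison is partly inferred.** This stands in part. The EQ5D is not a listed endpoint, and its stated use is the QALY calculation. Chronic pain may be analysed as a count, and the IPQ is a seven-level item. The case is therefore clearest for the EQ5D index.

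**The gain may be small.** This also stands. Surgery removes the condition measured at baseline, so r may be low; at r = 0.1 the gain over one-year values is 1%. The protocol allows as few as five operators per cadre, and adjusting for patient baseline does not remove differences between operators.

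**A stronger reading that the documents do not support.** A reader might infer that the two-sample test would also be applied before versus after surgery, treating paired values as independent. That would inflate the standard error by 1/√(1 - r), or 1.20 at r = 0.3 and 1.41 at r = 0.5. But the t-test sentence directly follows two comparisons of independent groups. The QALY and DALY text works from within-patient differences and promises only means. The plan contains no before-after standard error to be wrong.

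**Conclusion.** The point holds as a modest, nearly cost-free improvement. The only test named for continuous variables forgoes precision that the preoperative EQ5D and IPQ could supply. Against a t-test on one-year values, ANCOVA cuts the variance by 1%, 9% or 25% at r = 0.1, 0.3 or 0.5. Against a t-test on change it cuts it by 45%, 35% or 25%. These figures rest on assumed correlations and independent patients, and the change-score figures also on equal SDs. The document supplies neither r nor the SD.

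There is no bias, and no effect on the binary primary endpoint or on the 97 and 114 per group. Only secondary and economic outcomes are affected. The gain is best supported for the EQ5D index and less certain for the IPQ, whose analysis scale is not stated.

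**What to change.** Amend Data analysis in Protocol section 4.1 as follows.

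- Compare the one-year EQ5D index between cadres by linear regression on randomised cadre and the preoperative EQ5D index. Report the adjusted difference with its confidence interval.
- Do likewise for the IPQ with the preoperative IPQ as covariate, using an ordinal model if it is kept as a seven-level item.
- Keep the two-sample t-test for continuous variables that have no baseline measurement.
- Add one clarifying clause: any confidence interval reported for mean QALYs gained or DALYs averted is computed from the within-patient differences already described.

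The cost is wording only. The preoperative measurements are already planned, and neither the sample size nor the visit schedule changes.

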### ***Financial burden***

Sierra Leone ranks as 181 in the UN Human Development Index and 56.6% of the population live below the income poverty line (less than \$1.25 per day).(32)

Healthcare for pregnant, lactating women and children under 5 has been delivered free since 2010 in Sierra Leone. Besides free treatment for HIV, TB and Malaria, all other healthcare costs are paid by the patient, which is considered the main barrier to access healthcare.(33) Catastrophic health expenditure is defined in relation to a household's capacity to pay and occurs when the health costs exceed 40% of the total household expenditure.(34)(35)

Hernia repair in Sierra Leone costs between US\$ 50-75 and represents a vast financial burden that forces many into catastrophic health expenditure. Patients with hernias may also experience disability and potential loss of earnings. A 2013 cluster survey from Sierra Leone recorded that 20% of patients were unable to work due to their untreated hernias.(28) Furthermore, delay in seeking treatment for hernia is associated with higher morbidity and mortality and higher cost of emergency surgery in the event of strangulation.(36)

This project based in Sierra Leone will investigate how non-surgeon medical officers and surgical assistant CHOs can be trained to perform mesh hernia repair under local anaesthesia. The study will also compare outcomes between these two staff categories in order to detect any significant differences that will have to be taken into consideration for large-scale implementation of this hernia repair method in Sierra Leone and beyond. A cost-effectiveness analysis will also be undertaken. The Sierra Leone site contributes to a multicentre study on inguinal hernia repair in sub-Saharan Africa. It is part of a collaboration between multiple partnerships and builds on several years of research in African environments.(11,12,16,17)(23,26,27)

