### **3. Topics and objectives**

The purpose of this project is to assess low cost mesh inguinal hernia repair in Sierra Leone. The specific aims are to:

1. Evaluate feasibility and effectiveness of implementation of inguinal hernia repair using low cost mesh
2. Assess whether non-physician clinicians and doctors can deliver comparable outcomes in inguinal hernia repair using low cost mesh.
3. Analyse cost-effectiveness of inguinal hernia mesh repair in Sierra Leone.

These aims will be addressed by a single blinded, randomized clinical trial.

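### The trial is sized for non-inferiority with a 5-point limit, but the only analysis stated for binary outcomes is a test of no difference that never uses the limit

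*Protocol*

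**What the plan says.** **Sizing.** Protocol section 4.1, Sample size calculation, opens "Based on a non inferiority design the assumptions are as follows" and gives "80% power, 5% significance level", a "5% non-inferiority limit" and an "expected success rate of 98% in both arms". The result is 97 per group, raised to 114 per group (228 in total) for 15% loss to follow-up. It does not say whether the 5% significance level is one-sided or two-sided, and it does not define success.

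**Aim.** Section 3, Aim 2: "Assess whether non-physician clinicians and doctors can deliver comparable outcomes in inguinal hernia repair using low cost mesh".

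**Analysis.** Section 4.1, Data analysis, says that outcomes after surgery by doctors and by CHOs will be compared. The tests named are t-tests for continuous variables and, for binary outcomes, "Chi-square or Fisher exact test will be used for counts. A p-value < 0.05". The 5% limit does not reappear. No confidence interval, test against the limit or non-inferiority decision rule is given.

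**Endpoint.** The same paragraph says that primary endpoints "for patient data include hernia recurrence. Secondary endpoints include postoperative" complications. Physical examination for recurrence takes place at two weeks and at one year.

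**Framing.** The Introduction (Financial burden) says the study will "compare outcomes between these two staff categories in order to detect any significant differences" that would matter for large-scale implementation.

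**The concern.** A non-inferiority trial needs a rule that compares the plausible range of the difference with the limit. Chi-square and Fisher tests do something else: they look for evidence against equality. A non-significant result from them may mean that the cadres perform alike, or that the trial is too small to tell. With recurrence expected at about 2%, the second explanation is always available.

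The sample size and the analysis therefore answer different questions, and the analysis does not answer Aim 2. The protocol says that its results will inform national policy on hernia repair and on CHO training. It should be clear in advance what result would support task-shifting and what result would not.

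**Working it through.** **Inputs from the protocol.** 80% power, 5% significance level, 5% limit, 98% success in both arms, 97 per group, 15% loss.

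**Assumptions.** Success means no recurrence, the limit is 5 percentage points absolute, outcomes are independent (no clustering by operator), and the chi-square test is uncorrected.

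**1. Reproduce the sample size.**

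n = (z(1−α) + z(1−β))² × 2p(1−p) / limit²

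- One-sided 5%: (1.645 + 0.842)² × 2 × 0.98 × 0.02 / 0.05² = 96.9, so 97. This matches the protocol.
- One-sided 2.5%: (1.960 + 0.842)² × 0.0392 / 0.0025 = 123.1, so 124. This does not match.
- Loss: 97 / 0.85 = 114.1, against 114 stated. The rounding is immaterial.

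The sizing is thus a non-inferiority calculation at one-sided 5%. It corresponds to comparing the upper limit of a two-sided 90% confidence interval with 5 points.

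**2. The stated tests when CHOs are worse by the full limit.** True recurrence is 7% for CHOs and 2% for doctors. For every pair of recurrence counts, take its binomial probability and add up the probabilities of the pairs with p ≥ 0.05.

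| Evaluable per arm | Non-significant, chi-square | Non-significant, Fisher |
|---|---|---|
| 97 | 63.1% | 74.7% |
| 114 (no loss) | 56.3% | 67.4% |

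Power to detect a deficit as large as the limit is therefore only 37% (chi-square) or 25% (Fisher) at 97 per arm. A difference test with 80% power for 98% against 93% would need 269 per group.

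**3. An interval rule in the same situation.** With 97 per arm and 7% against 2%, the upper 90% limit falls below 5 points, wrongly passing, in 7.7% of trials with a Wald interval and 4.4% with a Newcombe interval. The nominal rate is 5%.

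**4. A worked example.** Suppose 7 of 97 CHO patients and 2 of 97 doctor patients recur.

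- Difference: 5/97 = 5.2 points.
- Chi-square p = 0.088 and Fisher p = 0.17, so neither is significant.
- Standard error: √(0.0722 × 0.9278/97 + 0.0206 × 0.9794/97) = 0.0300.
- Upper 90% Wald limit: 0.0515 + 1.645 × 0.0300 = 0.101, or 10.1 points, twice the limit.

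The stated test finds no significant difference, while the data are compatible with a deficit of twice the limit.

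**5. Power of the interval rule when the cadres are equal.** True recurrence is 2% in both arms, with 97 per arm.

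- Normal approximation, one-sided 5%: Φ(0.05/√(0.0392/97) − 1.645) = 80.0%.
- Exact enumeration, 90% interval: 80.7% with Wald, 63.7% with Newcombe.
- Normal approximation with a 95% interval: Φ(0.05/√(0.0392/97) − 1.960) = 70.1%.

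With about two events expected per arm, the choice of interval method matters.

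**The case against.** **The protocol never says that p ≥ 0.05 means comparable.** This stands. A reader might infer that a non-significant result will be reported as showing comparability, because Aim 2, the Introduction and the Data analysis paragraph offer nothing else to go by. It is still an inference. The sentence in the Introduction can equally be read as a search for problems that matter for implementation. So the 63% to 75% is the rate of non-significant results, and it becomes a rate of wrong conclusions only if the result is read in that way.

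**The test sentence is generic, and a decision rule may be left to the SAP.** The sentence covers all comparisons, follows directly on the comparison with other collaborating centres, and does not single out recurrence. An interval rule is often left to a SAP, which is not at hand here. This limits the point but does not remove it. The protocol is not silent: it names tests and a threshold for counts and does not exempt the primary comparison. A SAP that followed the Data analysis paragraph would ignore the limit, and one that followed the sample-size paragraph would depart from the Data analysis paragraph.

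**The result can depend on which test is chosen.** This also stands. With 7 against 1 recurrences of 97, Fisher gives p = 0.065 and uncorrected chi-square p = 0.030. That case therefore does not show that the stated analysis misses the excess. The 7 against 2 case is non-significant by both tests.

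**The endpoint wording is a separate matter.** Partly so. The open list of primary endpoints and the unnamed time point are not faults of the test. They matter here because the limit must apply to a defined quantity, and success is not defined.

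**Conclusion.** The point holds as a contradiction within the protocol: a non-inferiority sample size on one side, and on the other an analysis for binary outcomes that never uses the limit and cannot establish Aim 2. The sample size itself is sound for a one-sided 5% test.

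If CHO recurrence is truly 5 points higher (7% against 2%) with 97 per arm, the stated tests are non-significant in 63% to 75% of trials. A 90% interval compared with the limit would wrongly pass in about 4% to 8%. These figures rest on success meaning no recurrence, an absolute limit and no clustering by operator.

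The documents do not support the stronger claim that the investigators plan to treat non-significance as proof of comparability. They support only that no other criterion is given. Because this is the main between-cadre comparison and is meant to inform policy, it should be corrected before outcomes are seen.

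**What to change.** In section 4.1, Data analysis, give the primary comparison its own rule, for example:

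*The primary endpoint is hernia recurrence at the one-year physical examination; success is its absence. Non-inferiority of CHOs is concluded if the upper limit of the two-sided 90% confidence interval (one-sided 5%) for the CHO-minus-doctor difference in recurrence is below 5 percentage points, using [named method]. A non-significant chi-square or Fisher test is not evidence of comparability.*

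Keep the t-tests, chi-square and Fisher tests for secondary comparisons. In the sample-size paragraph, state that the 5% level is one-sided, that the limit is absolute, and that success has the meaning above. The one-year time point is a proposal that fits the follow-up schedule; the protocol does not fix it, so the sponsor should confirm it.

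**Cost.** One paragraph of text and no new data. No extra patients are needed at one-sided 5% on the normal approximation used for sizing. The stated 80% power should be restated for the method chosen: about 81% with Wald, whose false-pass rate at the limit is 7.7%, or 64% with Newcombe, whose rate is 4.4%. If a 95% interval is preferred, power at 97 per group is about 70% by the sizing formula, and 80% would need 124 evaluable per group, or 124/0.85 = 146 after 15% loss.
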